### The model of support

ACCHSs will be acknowledged as the experts in cultural healthcare for Indigenous peoples in their communities and Australia. The study also recognises the need for flexibility based on needs of individual services and of the ACCHS sector as a specialist sector overall. Support approaches will include the same core elements (table 1). However, approaches will be tailored to the needs of each ACCHS, for what works best for their service, clients and communities.

The core support elements were designed based on evidence-based approaches for supporting implementation of alcohol care.^21 29^ The project team also drew on their experience working within (six authors) and with Aboriginal health services; and in health workforce development (nine authors). Advice was also received from ACCHS peak organisations and networks in New South Wales and South Australia, and from a research team conducting a quality improvement trial for ACCHSs on diabetes screening.^42^

At the start of the early support phase, the support will be refined based on preliminary analysis of qualitative data from staff interviews and after feedback from the initial national workshop for early support service representatives. Tailoring and further minor refinement of support will occur during the trial, informed by service feedback.

Early support (‘intervention’) services will receive the support soon after the trial starts (1 year of active support, 1 year maintenance phase). Late support (wait-control) services will receive the same intervention elements 2 years after the start of the early-support phase. Due to the nature of the intervention, it is not possible to blind participants or staff as to which services are receiving support.

Identifying service championsEach service will be asked to identify two staff representatives to work collaboratively with their service staff and the research team on increasing alcohol care. Services will be asked to consider nominating a clinician, Aboriginal health professional and/or an individual from management. Service champions will be invited to attend an initial national face-to-face workshop, and second monthly teleconferences. These meetings will ensure that support approaches are in line with the values of each ACCHS, and will allow sharing of expertise and initiatives. Champions will be key in highlighting the potential benefits of change in their service and will encourage service staff to discuss their second monthly data feedback, and to address any key barriers to change.^43^
WorkshopsA national workshop will be held at the beginning of each support phase to bring champions from those services together for capacity building and networking. Feedback will be obtained from champions about pre/post-workshop knowledge, training preferences, priority areas for support and useful resources. Key presentations from workshops will be video-recorded and made available via a password-protected website.A wrap-up workshop will be organised for early support service champions (only) at the end of their support phase. Opportunities will be provided for service champions to provide verbal and written feedback on support, to discuss continuing quality improvement approaches and to network. Study results to that point will be discussed.Onsite trainingTraining will be offered at each service for all staff, with maximum duration of 2 days. Core elements will include screening, alcohol and the body, brief intervention and treatment approaches, including relapse prevention medicines. Due to the individuality of each service, flexibility will be given to allow inclusion of other (alcohol-related) training topics. The training will be co-facilitated by an addiction specialist (KC) and an Aboriginal researcher with clinical background ([name]) and will use culturally specific content and resources. Training content will be aligned with Indigenous protocols such as gender appropriateness, kinship systems and cultural obligations; such a family and community sharing which at times can impact on substance use.^27 44^ Pre/post-training feedback will be collected from participants.Resources/fundingThe trial will provide several hard copy and electronic resources for free to services (ie, the Handbook for Aboriginal Alcohol and Drug Work,^45^ Alcohol Awareness Kit^46^ and Quick Reference Guide to the Treatment of Alcohol Problems^47^).Each ACCHS will be provided with funding to purchase additional resources. Services can choose, in partnership with the chief investigators, how they spend their funding. The early support arm of the project will receive up to $9000 for resources. The late support arm will receive up to $3500. This is a reduced sum as they will have access to resources developed within the early support phase, so time and development costs will be less. Resources must be alcohol-related and may include additional training, conference attendance, education resources for staff or clients, funds for health promotion events or for local adaptation of resources.Practice software supportA Communicare support officer will be available during the trial to support ACCHSs with the practice software. Some ACCHSs may choose to make modifications to Communicare to make alcohol ‘clinical items’ more accessible for staff. One example is adding AUDIT-C into the Aboriginal and Torres Strait Islander (Indigenous) health assessment (‘Adult Health Check’), which was not routine in standard versions of Communicare at the time of trial commencement. AUDIT-C can also be added to other regular assessments such as antenatal and the pre-consult examination (ie, routine observations and/screening by a nurse or Aboriginal health worker before seeing the doctor). Services will also be provided with information about existing fields (‘clinical items’) available on Communicare for recording episodes of alcohol care (education/advice; on-site counselling), which can then be retrieved by data extraction.Second monthly data feedbackIndividual services will receive feedback on their routinely collected data on alcohol care every 2 months during their support phase. Data will be represented visually using images and or graphs (figure 3) and be fed back to nominated staff, including champions. Services will be asked for feedback on the data representation early in the support phase and adaptions will be made as requested. Services will be encouraged to discuss the results among staff, to see if there are ways to further improve alcohol screening and treatment rates.Phone conferencesSecond monthly phone conferences will be organised for service champions. These will provide the opportunity for ACCHSs to network nationally. The champions will be split into two groups for the phone conferences, based on remoteness. During teleconferences, champions can discuss their data feedback, progress, successes, difficulties, helpful tools, resources or approaches.Online platformA password-protected web portal will allow ACCHS staff to access and share current evidence, culturally appropriate resources and to network. It will include a discussion board. Short videos, training presentation slides and clinical protocols will be uploaded by project staff.

**Figure 3 F3:**
[figure not shown]
Three of the elements used to feedback alcohol screening data to ACCHSs.

### Data collection

#### Qualitative data

Qualitative data will be collected from ACCHSs at the start of the early support arm. The data will help inform the support model. Structured phone interviews will be conducted with approximately five staff members from each ACCHS in the early support arm, with the aim of a total of 50. Champions and/or key staff will be approached to assist with recruiting interviewees.

Alcohol can be sensitive to discuss due to cultural protocols such as kinship/family systems, gender or age, shame (embarrassment) or community and social acceptance of alcohol.^48–50^ Therefore, the interview questions will be framed using a strengths-based, capacity-building approach.^51^ Interview questions will include approaches to make it easier to talk about alcohol, treatment around alcohol, skills and knowledge needed to provide quality alcohol care, new ways of helping people who struggle with alcohol, other successful programmes that could be used as a model for alcohol care and ideas for improvement in alcohol care.

Interviews will be conducted by two Indigenous staff with experience working with ACCHS and conducting interviews. One interviewer will facilitate the interview while the other will live-transcribe. The interviewers will compare and discuss notes after each interview. Memos will also be written by the lead author ([name]) on each interview.

#### Quantitative data

Non-identifiable data on episodes of screening, alcohol care and related variables (see below) will be extracted from the Communicare database of each ACCHS on the 28th day of every second month throughout the 5-year trial (figure 4). The baseline extraction will include data for 12 months before the trial starts. Participating services use structured query language (SQL) queries developed for this project to extract routinely collected data. For every 2-month period a denominator sheet will be extracted which includes the date of the last visit for each client who has attended during that period and their gender and age. In addition the following variables will be extracted, each one linked to an individual client ID and the date the variable was recorded: AUDIT-C responses; the clinicians’ perception of the client’s drinking status (‘Ex-drinker’, ‘Non-drinker’, ‘Within safe drinking limits’ or ‘Unsafe - needs intervention’); whether a brief intervention, or a counselling session for alcohol use was provided; whether a relapse prevention medication was prescribed (ie, acamprosate, naltrexone or disulfiram); and if measured, a range of biological markers which may be affected by alcohol consumption (BP, HbA1C and GGT).

**Figure 4 F4:**
[figure not shown]
Project timeline: SPIRIT schedule of enrolment, interventions and assessments for the trial.

A spreadsheet will track dates when key elements of support are provided to each service. Staff numbers attending training and participating in teleconferences will be recorded.

#### Service retention and withdrawal

Regular contact will be made with services during their support phase through the second monthly teleconferences (by KC and often [name]), and for the purposes of data extraction (by BH). Effort will be made to address any concerns or suggestions, and to minimise burden of participation on services. However, services may withdraw from the study, for any reason and at any time.

#### Data storage and confidentiality

De-identified data will be sent to the project team every 2 months (by email or Cloudstor). Data will be stored securely in a University of Sydney drive only accessible by relevant members of the research team. Identification numbers rather than names are used for services in the data set and in reporting. Data will stored for 7 years after the last publication on the study.

### Analysis

#### Qualitative

Two independent analyses of the qualitative data will be conducted: analysis of the memos and of the transcripts. This complementary analytical strategy aims to enhance examination of the raw data in the formation of key concepts.^52^

Interview transcripts and memos will each be imported into the qualitative software, NVivo V.11. Memos will be analysed by the lead interviewer ([name]). Transcripts from the structured interviews will be analysed by an independent research associate to produce key themes. This involves the interpretation of descriptive data to explain the meanings of the interviewees’ responses.^53^ Each data set will be coded separately using a process of constant comparison.^53^ This will involve coding and organising like data into categories along with a comparison and interpretation of emerging themes across all transcripts and memos.^54^ A team of relevant experts will meet to discuss both analyses and find consensus on key themes and sub-themes. These key themes and findings will be described.

#### Quantitative

Only the routinely collected data on Indigenous Australian clients aged 16+ years who have attended a participating ACCHS in the last 12 months will be included in analysis to assess:

The odds of a client being screened using AUDIT-C at least once in any 2-month period (considering those who attend in that period).The odds of a client being recorded as receiving treatment for unhealthy alcohol use at the ACCHS, including advice/education or counselling, relapse prevention medicines.The number of clients identified by ACCHS staff to have unhealthy alcohol use:via AUDIT-C: using cut-offs recommended for ACCHSs by the Australian Institute of Health and Welfare (3+ for a woman, 4+ for a man).^23^
and/or staff perception of drinking status (eg, safe, unsafe, non-drinker or ex-drinker).

We will use statistical packages, IBM SPSS for descriptive analyses and R for multi-level modelling.

Multi-level modelling will be used to account for clustering of observations under clients, who are nested within services. We will assess if clients are more likely to be screened for risky alcohol-use and provided with treatment if they are attending a service receiving support.

Two dummy variables will be constructed to indicate whether or not clients were screened with the AUDIT-C during each 2-month data extraction period, or if they received treatment. These variables will be used as outcomes in multi-level logistic regressions. As data are aggregated at bimonthly intervals, repetitive screenings within those 2-monthly periods will not influence the modelled effect of the intervention. However, to ensure that the intervention is associated with increased odds of appropriate screening, we will create a dummy variable indicating whether a client has been screened in the previous 12 months, and use this variable as the outcome in a multi-level logistic regression.

Characteristics of ACCHSs, such as number of clients, will be compared descriptively between the early/late-support services. Characteristics that display major imbalance between arms will be considered as adjustment factors in outcome analyses. As data are collected as part of routine clinical activity, missing data are likely to be non-random, as such multiple imputation will not be performed.

All analyses will be repeated for the maintenance phase of the study to see if study effects weaken or strengthen over time. The analysis will also be repeated after the late support services have received support, to see if any effect on use of screening or treatment can be replicated.

If a significant effect of the support on alcohol care outcomes is demonstrated, a secondary analysis will examine the elements of support which were most effective, and whether the effect of support changed over time during a support phase. Potential change in client health indicators over time (AUDIT-C scores, GGT, HbA1C, BP) will be examined in relation to support provision.

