#### Sample size

Sample size requirements were calculated using PASS (Power Analysis and Sample Software).^36^ Because larger numbers are needed to be able to determine increases in treatment provision than to demonstrate an increase in screening, the treatment provision outcome was used for sample size calculation. In an ACCHS of 1000+clients per year, approximately 60% (n=600) are likely to be aged 16 years or older.^37^ We estimate that 57% of clients (n=342) have likely been screened for alcohol use within 12 months^16^ and at least 25% (n=86) of screened clients are likely to be drinking above NHMRC recommended limits.^14 38 39^ In the late support arm, it is likely that 60% (n=51) of identified unhealthy drinkers will have an alcohol intervention recorded.^16^ Assuming an intra-cluster correlation coefficient of 0.04,^40 41^ enrolling 10 early support services and 10 late support services will allow for an increase in treatment provision over a 12-month period of at least 13% in the early support services to be detected (ie, from 60% to 73%; 80% power and 2-sided significance of 0.05). We will enrol an additional service in each arm to allow for the possibility of clusters dropping out of the study. Accordingly, the target number of services to be enrolled is 22.

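### The stated client-and-service hierarchy has no service-by-period variation, so any model in which a service's support status changes over time would mistake ordinary service drift for an effect of support

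*Protocol article*

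**What the plan says.** All passages are in the protocol article; no separate analysis plan is shown.

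- **Clustering.** The Quantitative analysis section states "Multi-level modelling will be used to account for clustering of observations under clients, who are nested within services". The clustering levels are therefore client and service.
- **Outcome and model.** One indicator records "whether or not clients were screened with the AUDIT-C during each 2-month data extraction period"; a second records treatment. "These variables will be used as outcomes in multi-level logistic regressions".
- **Exposure.** The models ask whether clients are more likely to be screened and "provided with treatment if they are attending a service receiving support". For any one service this status changes during the trial.
- **Repeats.** The analyses are run again for the maintenance phase, and "The analysis will also be repeated after the late support services have received support".
- **Data span.** The Quantitative data section describes extraction every second month for five years, with a baseline extraction reaching back 12 months. Whether the baseline months enter the main model is not said.
- **Size.** The Sample size section says "enrolling 10 early support services and 10 late support services will allow for an increase in treatment provision" from 60% to 73% with 80% power. One service per arm is added, so "the target number of services to be enrolled is 22".

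The article names R for the multilevel models. It gives no estimator, test statistic or degrees of freedom.

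**The concern.** Support is delivered to services, so the evidence about it lies in how services differ and how they change. A constant service intercept captures how far a service sits above or below the others. It does not capture that one service's screening rate rises while another's falls for reasons unrelated to support.

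This does limited harm when early and late services are compared within a single phase. It matters when a service's own earlier and later periods are set against each other. The constant intercept then drops out of the contrast, and a model with many client records treats the remaining service-level movement as signal.

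The repeat after late support is the most exposed analysis. Late services start support two years after the early arm, so by then every service has been offered it and no never-supported arm runs alongside. A natural replication would compare late services with their own past.

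The document also gives a reason to expect uneven drift. The Introduction reports that AUDIT-C became a national performance indicator for these services in July 2017, after the first enrolment date of 28 October 2016 in Table 2. Services may well have taken it up at different speeds. At stake is a replication, or a pooled before-and-after result, that appears significant through drift alone.

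**Working it through.** **1. The plan's own power figure.** Inputs from the Sample size section: 60% v 73%, ICC 0.04, 86 unhealthy drinkers per service, 10 services per arm, two-sided 0.05.

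- Design effect = 1 + (86 − 1) × 0.04 = 4.40.
- SE = √[(0.60×0.40 + 0.73×0.27) × 4.40 / 860] = √(0.4371 × 4.40 / 860) = 0.0473.
- 0.13 / 0.0473 = 2.75, and normal power = Φ(2.75 − 1.96) = 78.5%. This is close to the stated 80%, so the figure is essentially reproduced on normal theory.
- On a noncentral t with 18 df, the same inputs give 73.9%.
- With 11 services per arm, SE = 0.0451 and the ratio is 2.88. Power is 82.2% on the normal and 78.3% on t with 20 df.

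**2. A model that spans a change in support.** Take two periods, 11 services per arm, *m* clients per service and period, equal sizes, and records independent between periods. Let ρ be the ICC and *c* the correlation of a service's level between periods. In units of p(1 − p):

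- true variance of a service's change = 2ρ(1 − c) + 2(1 − ρ)/m;
- variance seen by a model with only a constant service intercept = 2(1 − ρ)/m;
- ratio R = 1 + mρ(1 − c)/(1 − ρ);
- true error of a nominal 5% z test = 2 × P(Z > 1.96/√R).

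For example, with m = 86 and c = 0.9, R = 1 + 86×0.04×0.1/0.96 = 1.36, and the error is 2 × P(Z > 1.68) = 9.3%.

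| c (assumed) | m = 86: R | error | m = 600: R | error |
|---|---|---|---|---|
| 1.0 | 1.00 | 5.0% | 1.00 | 5.0% |
| 0.95 | 1.18 | 7.1% | 2.25 | 19.1% |
| 0.9 | 1.36 | 9.3% | 3.50 | 29.5% |
| 0.8 | 1.72 | 13.5% | 6.00 | 42.4% |

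The value 86 is the plan's cluster size for treatment. The value 600 is its count of clients aged 16 or over per service, the scale relevant to screening. The plan gives no ICC for screening, so 0.04 is carried over as an assumption.

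A simulation fitted the random-intercept logistic model by maximum likelihood (22 services, m = 86, 600 runs per setting). It gave 5.5%, 9.7% and 13.5% at c = 1, 0.9 and 0.8. A t reference on 20 df lowered these to 4.0%, 7.3% and 11.2%. A small-sample reference alone therefore does not cure the problem, because the variance term itself is absent. A simulated test on service-level changes held about 4% to 5%.

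**3. A comparison of arms within one phase.** With K = 22 services and 20 df, an uncorrected z test has these errors:

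- REML-type variance: 2 × P(t₂₀ > 1.96) = 6.4%.
- Maximum likelihood: 2 × P(t₂₀ > 1.96 × √(20/22)) = 7.6%.
- Simulated logistic model: 6.6% with z (Monte Carlo SE 0.5 points), and 5.0% with t on 20 df.

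**The case against.** The strongest reply is that the article fixes too little to be charged with an invalid test. It names no estimator, reference distribution or degrees of freedom, and it rules none out. A condensed protocol commonly leaves these to an analysis plan, and that plan is not shown. It also never says that baseline data enter the main model; its overview presents two randomised arms, support against usual care. Within one phase the service intercept carries most of the relevant variation. The autocorrelations come from outside the document, and 600 clients is paired with an ICC given for a different outcome. The power figure concerns treatment provision, a secondary outcome, and the plan says screening needs smaller numbers.

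Most of this stands. A reader might infer that no small-sample correction will be used, or that the main comparison runs above 5%. The documents support neither: the first is silence, and the second requires an uncorrected z test that is nowhere stated. An error of 9.3% can be obtained for 22 services, but only with maximum likelihood plus two stratum terms that the plan does not state.

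The reply does not remove the structural point. The clustering levels are stated, not left open, and they are client and service. Applied as written to a model in which support starts within services, they omit the variation that such a contrast depends on.

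**Conclusion.** The point holds in conditional form. For any model that spans a change in a service's support status, the stated hierarchy understates the uncertainty of the support effect unless service levels move perfectly together over time. For autocorrelations of 0.95 to 0.8, true error is roughly 7% to 13% at 86 clients per service and 19% to 42% at 600. These sizes rest on assumed autocorrelation, an ICC of 0.04 for both outcomes, equal service sizes and a two-period simplification. They show a range and are not a forecast.

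The randomised comparison within one phase is not shown to be invalid. Its possible excess is small and depends on a test that the article does not specify.

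Restating the power is a valid but minor correction. The drop from the stated 80% to about 74% is not all due to the t reference, since the normal calculation already gives 78.5%. With all 22 services retained, the t-based figure is about 78%.

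**What to change.** - In every model in which support status changes within a service, add a service-by-period random effect or service-specific time slopes. Alternatively, test the support effect on service-level changes. State that this covers the repeat after late support, and the main model if baseline months are pooled into it.
- Name a few-cluster reference for the support effect: t on the number of services minus the number of service-level parameters, or a permutation of services within remoteness strata.
- Restate the power for 60% v 73% on that basis: about 74% with 10 services per arm and 78% with 11.

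The cost is a few sentences in the analysis plan, a little programming and somewhat wider confidence intervals. No change to recruitment or data extraction is needed.

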**Outcomes and analysis:**

Primary outcome is use of screening using AUDIT-C as routinely recorded on practice software. Secondary outcomes are recording of brief intervention, counselling, relapse prevention medicines; and blood pressure, gamma glutamyltransferase and HbA1c. Multi-level logistic regression will be used to test the effectiveness of support.

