The primary outcome will be routinely collected data on screening rates using AUDIT-C. Secondary outcomes will include recorded delivery of brief intervention, counselling or prescribed medicines to reduce relapse in alcohol dependence. We will also describe changes in reported drinking and in biological measures that can be affected by drinking such as gamma glutamyltransferase (GGT, a liver enzyme),^33^ HbA1C^34^ and systolic blood pressure (BP).^34^

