### Protocol amendments

The trial’s registration data are shown in table 2. Any necessary protocol amendments will be agreed on by study investigators, and where appropriate, participating services. Then they will be registered with the Australian and New Zealand Clinical Trials Registry.

**Table 2 T2:** WHO trial registration data

Data category	Information
Primary registry and trial identification number	Australia New Zealand Clinical Trials Registry: ACTRN12618001892202
Date of registration in primary registry	21/11/2018
Secondary identifying numbers	APP1105339
Sources of monetary or material support	NHMRC, Australia
Primary sponsor	The University of Sydney
Secondary sponsor	Royal Prince Alfred Hospital
Contact for public and scientific queries	[name], FAChAM, FAFPHM, PhD [contact]
Public title	Supporting Aboriginal community controlled health services to deliver alcohol care: a cluster randomised controlled trial
Scientific title	Increasing uptake of evidence-based management of unhealthy alcohol use in Aboriginal primary healthcare services: a cluster randomised controlled trial
Counties of recruitment	Australia
Health condition(s) or problem(s) studied	Hazardous alcohol use; alcohol use disorders
Interventions	Health service support (including training, sharing learning between services); regular data feedback
Key inclusion or exclusion criteria	Health services: are Aboriginal Community Controlled Health Services deliver care to at least 1000 unique clients annually use ‘Communicare’ as their practice software Data from clients 16 years and older are eligible for extraction
Study type	Interventional; Allocation: randomised; Primary purpose: prevention; Cluster randomised trial
Date of first enrolment	28/10/2016
Target sample size	22 services
Recruitment status	Complete
Primary outcomes	AUDIT-C screening rate
Key secondary outcomes	Brief intervention for alcohol rate

AUDIT-C, Alcohol Use Disorders Identification Test-Consumption; NHMRC, National Health and Medical Research Council.

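### Treatment is modelled only as one pooled indicator, so the registered key secondary outcome, the brief intervention rate, has no matching analysis

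*Protocol article*

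**What the plan says.** The Quantitative part of the Analysis section sets the modelled outcomes as two indicators, for whether clients were "screened with the AUDIT-C during each 2-month data extraction period, or if they received treatment", and adds: "These variables will be used as outcomes in multi-level logistic regressions". The treatment question is a single one: "The odds of a client being recorded as receiving treatment for unhealthy alcohol use at the ACCHS, including advice/education or counselling, relapse prevention medicines". The only further indicator is for screening in the previous 12 months. The rest of the section repeats the analyses in later phases, looks at which support elements worked best, and examines change in health indicators. None of this splits treatment by type.

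Elsewhere the treatment outcome is described in different ways:

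- Table 2, under Protocol amendments, gives the key secondary outcome as "Brief intervention for alcohol rate".
- The abstract states: "Secondary outcomes are recording of brief intervention, counselling, relapse prevention medicines".
- The Methods overview states: "Secondary outcomes will include recorded delivery of brief intervention, counselling or prescribed medicines to reduce relapse in alcohol dependence".
- The Sample size section powers the trial on treatment provision, meaning that any alcohol intervention is recorded.
- The Quantitative data section extracts brief intervention, counselling and prescribed medicines as separate items, each tied to a client and a date.

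**The concern.** A registered key secondary outcome should have a named analysis. Here the article says which variables enter the regressions, and brief intervention alone is not among them. When results are reported, the team would have to present the pooled outcome under the brief intervention label or add a model after seeing data. Either choice weakens the claim to prespecification.

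The second issue is interpretation. The pooled indicator is positive when any one of three quite different kinds of care is recorded. A higher rate in the early support arm would show that something more was recorded, but not what. This matters because the support itself includes guidance on the software fields for advice/education and on-site counselling, "which can then be retrieved by data extraction". The components may therefore respond differently to better recording and to better care, and a single pooled estimate cannot show whether they do.

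**Working it through.** **1. Which outcomes are modelled.**

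| Outcome | Named as | Own model described? |
|---|---|---|
| AUDIT-C screening, two-month | Primary (abstract, Table 2) | Yes |
| AUDIT-C screening, previous 12 months | Check on appropriate screening | Yes |
| Any treatment | Basis of the sample size | Yes |
| Brief intervention | Key secondary (Table 2) | No |
| Counselling | Listed in abstract and overview | No |
| Relapse prevention medicines | Listed in abstract and overview | No |

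The wording also differs: the analysis section says advice/education where the abstract, overview and Table 2 say brief intervention.

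**2. The plan's own power figure, to see which outcome it belongs to.** Inputs from the Sample size section: 86 identified drinkers per service, intra-cluster correlation 0.04, 10 services per arm, 60% against 73%, two-sided 0.05.

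- Design effect = 1 + (86 − 1) × 0.04 = 4.40.
- Effective n per arm = 10 × 86 / 4.40 = 195.5.
- Standard error (unpooled) = √[(0.60 × 0.40 + 0.73 × 0.27) / 195.5] = √(0.4371 / 195.5) = 0.0473.
- Power = Φ(0.13 / 0.0473 − 1.96) = Φ(0.79) = 0.785. The version with a pooled null variance gives 0.779.

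This agrees with the stated 80% to within about two points. The 60% is the rate for any recorded alcohol intervention, so the figure describes the pooled outcome only.

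**3. What one component could detect.** The documents give no component rates. Assuming control rates from 2% to 60%, the same cluster size, correlation and number of services, and 80% power (pooled null variance):

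| Assumed control rate | Detectable difference, alpha 0.05 | Alpha 0.05/3 |
|---|---|---|
| 2% | 6.3 points | 7.7 points |
| 10% | 10.2 | 12.0 |
| 30% | 13.7 | 15.9 |
| 40% | 14.1 | 16.3 |
| 60% | 13.3 | 15.3 |

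Three unadjusted tests, if independent, would have a family-wise error of 1 − 0.95³ = 0.143.

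**4. How the pooled indicator relates to its parts.** It is the union of the three. With the other two held fixed, a rise of x points in one component moves the union by between 0 points (those clients already have another treatment recorded) and x points (none of them has). As an illustration with assumed rates, medicines rising from 2% to 4% would move the pooled outcome by 0 to 2 points, against a planned detectable difference of 13. In the other direction, a move from 60% to 73% could come wholly from newly recorded advice or from any mixture. The pooled model returns the same estimate in each case.

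**The case against.** The case for leaving the plan alone is substantial. Pooling is its consistent idea: the abstract's methods paragraph puts the three kinds of care under treatment provision, the overview joins them with 'or', and the sample size rests on any recorded intervention. The abstract's list of secondary outcomes can be read as one group or as three items. The count of two indicators is not exhaustive, since a third follows for 12-month screening. Component breakdowns are often left to an analysis plan, and none is shown here. All of this stands as a defence of the pooled outcome. It does not supply an analysis for the outcome in Table 2, because the article itself says what the treatment regression is run on and the added indicator concerns screening.

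A reader might go further and infer that the pooled outcome is wrong, that brief advice will dominate it, or that a gain in medicines would be invisible. The documents do not support these readings. They give no component rates. The components are extracted separately and the plan provides for descriptive analyses, so a gain in medicines could still be described. That medicines are less exposed to recording changes is a reasonable inference, but it is not stated.

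Nor would a separate medicines model be decisive. For the assumed 2% to 4% change, the standard error is √[(0.02 × 0.98 + 0.04 × 0.96) / 195.5] = 0.0172, and power is Φ(0.02 / 0.0172 − 1.96), or about 21%. These medicines are also described as being for alcohol dependence, so identified drinkers as a whole may be a poor denominator.

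**Conclusion.** The point holds in a limited form. The registered key secondary outcome has no matching analysis in the article, and the pooled treatment outcome cannot show which type of treatment changed. Both follow from the text and need no assumed rate. Each component still counts within the pooled outcome, so none is wholly unexamined; what is missing is a separate model, above all for brief intervention.

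The primary outcome and the sample size are unaffected. The component figures (6.3 to 14.1 points at alpha 0.05) rest on assumed control rates and on carrying over 86 clients per service and a correlation of 0.04, so they indicate scale only. The plan should be corrected before results are seen.

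**What to change.** Keep the pooled any-treatment outcome and its model. Add an indicator for brief intervention alone, analysed with the same multi-level logistic regression, and name it as the registered key secondary outcome. Choose one term for advice/education and brief intervention and use it in the abstract, overview, analysis section and Table 2.

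Report counselling and relapse prevention medicines separately by arm, as estimates with confidence intervals. Label them supportive, and state the client group used as the denominator for medicines.

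The cost is one to three extra models on variables already extracted, with no new data collection. The components would have no stated power, medicines data would probably be sparse with wide intervals, and multiplicity would rise somewhat, which is why counselling and medicines should stay supportive. Rewording Table 2 to name the pooled outcome would also remove the inconsistency, but it would change a registered outcome and would still leave the type of treatment unidentified.
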